### Statistical analysis

Stata Corp. IC Version 16.1 will be used for all statistical analyses. Normally distributed continuous data will be presented as means with standard deviations (± SD). Continuously skewed data will be reported as medians with interquartile ranges (IQR). We will express categorical data as numbers and percentages. For intergroup comparisons, the student’s unpaired t-test and one-way analysis of variance (ANOVA) with Fisher’s test will be used for continuous variables and the chi-square test for categorical variables. Demographic and clinical profiles will be presented in frequency tables. Univariate and multivariate cox regression analyses will be used to determine the baseline clinical predictors of mortality. Survival curves generated by the Kaplan-Meier method will be used to determine the crude one-year survival among the different reperfusion groups and compared with log-rank tests. All variables will be expressed with their hazard ratio and 95% confidence intervals. For all tests, a p-value < 0.05 will be considered statistically significant.

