**Discussion:**

This study provides insights into the demographic, risk factors and clinical profiles of individuals with STEMI in South Africa. Its findings may improve the risk stratification, prognostication, and therapeutic management of STEMI patients in our setting. By comparing the clinical outcomes between the different coronary reperfusion strategies, our results may guide clinicians in providing better patient treatment, particularly in sub-Saharan Africa, where access to percutaneous coronary intervention may be limited. Furthermore, the study offers insights into the routine use of baseline serum uric acid as a potential low-cost prognostic biomarker of all-cause mortality in STEMI. Finally, this study’s findings may be of public health significance to local policymakers to aid in reinforcing primary prevention strategies and developing structured referral networks for timely coronary reperfusion of acute STEMI.

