## Methods

### Study aims

This study aims to determine the clinical outcomes of an acute STEMI within one year of clinical presentation to the division of cardiology at the CMJAH. The study also evaluates the association between baseline serum cardiac biomarkers of myocardial infarction and all-cause mortality within a year of acute STEMI.

The primary objective is:

To determine the all-cause mortality rate of an acute STEMI at 30 days, three and six months, and one year after the index presentation.

The secondary objectives include:

To determine the rates of cardiac-related re-hospitalisation, heart failure, angina, major bleeding, thromboembolism, non-fatal arrhythmias (namely, atrial fibrillation, ventricular tachycardia, and complete heart block) and planned or unplanned repeated revascularisation at 30 days, three and six months and one year after the index STEMI at CMJAH.To assess the relationship between all-cause mortality and the peak serum hs-cTnT, CRP and SUA measured on admission.To describe the baseline clinical characteristics of STEMI patients in our setting.To compare the clinical outcomes between STEMI patients who received thrombolysis, PCI, a pharmaco-invasive strategy and those who underwent no reperfusion at 30 days, six and three months, and one year after the index STEMI.To determine the baseline clinical predictors of all-cause mortality at 30 days, three months, six months and one year after the initial STEMI.To describe the adjuvant medical care provided and medication compliance rates at 30 days, three months, six months and one year after the index discharge from the hospital.

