### Study design and setting

The study is a single-centre, observational, prospective cohort of all consecutive individuals with an acute STEMI diagnosis presenting to the CMJAH. The study will take place in the division of cardiology at the CMJAH, a academic state-owned tertiary PCI-capable healthcare facility in Johannesburg, South Africa. Participants will be followed over one year, and clinical outcomes will be measured at 30 days, three months, six months and one year from the index date of hospital discharge. The first day after hospitalisation will be considered day one of the follow-up.

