### Data collection

Research data will be collected from 01 May 2021 to 30 October 2022. The Primary Investigator (PI) will use the Research Electronic Data Capture (REDCap) software as the primary data collection tool. At baseline, the PI will capture demographic, clinical, calculated TIMI and GRACE scores, laboratory test results, ECG, echocardiographic, coronary angiographic, revascularisation and discharge medication data shown in Appendix B. The PI will create and access a reference list of the study participants’ hospital numbers and specific study numbers. The PI will retrieve these from the relevant progress notes, National Health Laboratory Service (NHLS) lab track, electronic medical records, and coronary angiogram report database of the division of cardiology at CMJAH.

The PI will telephonically contact all participants or their designated family members to monitor general well-being, medication compliance, outpatient cardiac clinic visits and cardiac-related re-admissions. When re-admitted to CMJAH, the PI will access the relevant hospital records to ascertain whether our study’s outcomes of interest occurred. Participants will be deemed compliant with medication if they say so during the telephonic interviews. The telephonic interviews will follow a closed-ended structured questionnaire, as depicted in Appendix C. Each participant will receive a telephonic interview call at 30 days, three months, six months and twelve months after the index hospital discharge date. All participants will be given the PI’s phone number and business card and encouraged to save the number on their cellphones when they sign informed consent forms so that doctors from other hospitals can contact the PI for cardiac-related referrals to CMJAH.

The PI will obtain the peak values of serum hs-cTnI, serum CRP and SUA from routine blood tests drawn at baseline for all participants. Automated messages generated through REDCap will be sent to remind both the PI and the participants of their scheduled outpatient clinic visits a week before the visits.

An experienced research sonographer will perform standardised echocardiograms during the outpatient clinic visits three months and one year after the index discharge. The two cardiologists who supervise the study will verify all echocardiograms. Appendix D shows the left ventricular parameters and valve analysis that will be recorded.

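### The four reperfusion groups are not randomised, yet the stated comparison is crude Kaplan-Meier with log-rank tests, and no adjustment of that contrast for measured baseline risk is stated

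*Protocol article*

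**What the plan says.** All references are to the protocol article.

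- **Objective.** Study aims lists, as a secondary objective: "To compare the clinical outcomes between STEMI patients who received thrombolysis, PCI, a pharmaco-invasive strategy and those who underwent no reperfusion", at four time points up to one year.
- **Design.** Study design and setting: "The study is a single-centre, observational, prospective cohort of all consecutive individuals with an acute STEMI diagnosis". Treatment group is observed, not assigned.
- **Method for this comparison.** Statistical analysis: Kaplan-Meier curves "will be used to determine the crude one-year survival among the different reperfusion groups and compared with log-rank tests". Intergroup comparisons otherwise use the t-test, one-way ANOVA and "the chi-square test for categorical variables".
- **Multivariable model.** Same section: "Univariate and multivariate cox regression analyses will be used to determine the baseline clinical predictors of mortality". No sentence puts reperfusion group into this model.
- **Available risk scores.** Data collection: at baseline "the PI will capture demographic, clinical, calculated TIMI and GRACE scores".
- **Intended use.** Abstract, Discussion: "By comparing the clinical outcomes between the different coronary reperfusion strategies, our results may guide clinicians in providing better patient treatment". The hypothesis at the end of the Background speaks of similar mortality and morbidity benefit whichever revascularisation strategy is used.
- **Acknowledged limits.** The Discussion concedes that unmeasured confounders may not be controlled. It does not mention measured ones.

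**The concern.** The Background itself describes reperfusion choice as depending on the patient's circumstances. It ties primary PCI to time since symptom onset and to how quickly the procedure can be done. It ties fibrinolysis to a time window, to early PCI not being possible and to the absence of contraindications. It also reports long patient and transport delays locally. Groups formed in this way may well differ in prognosis before any treatment effect.

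A crude log-rank test asks whether survival differs between the groups as they happen to be made up. It cannot separate treatment from case-mix. If higher-risk patients cluster in one group, the test can show a difference that treatment did not cause, or mask one that it did. The second possibility matters here because the hypothesis is one of similar benefit, so a non-significant crude test could be taken as support for it.

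This is more than detail left to an unseen analysis plan. The article names the method for this comparison and describes the resulting estimate as crude.

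**Working it through.** The plan gives no effect size or power for this comparison, so there is no figure to reproduce. The check asks how large a purely case-mix difference could be.

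**Inputs from the article**
- Median predicted one-year mortality by GRACE 2.0 group: low 1.6%, moderate 2.8%, high 5.9% (Background).
- Sample size: 355 (Study sample size calculation).
- One-year mortality in the South African registry 6.7%; overall death rate at another sub-Saharan centre 10.4% (Background).

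**Assumed:** the risk mix in each group. The article gives neither group sizes nor GRACE distributions by strategy.

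**Step 1. Crude mortality with no treatment effect.** With a share h at high risk and the rest at low risk, crude mortality = h × 5.9% + (1 − h) × 1.6%.

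| Assumed high-risk share | Group 1 | Group 2 | Ratio |
|---|---|---|---|
| 50% v 30% | 2.95 + 0.80 = 3.75% | 1.77 + 1.12 = 2.89% | 1.30 |
| 60% v 20% | 3.54 + 0.64 = 4.18% | 1.18 + 1.28 = 2.46% | 1.70 |
| 70% v 20% | 4.13 + 0.48 = 4.61% | 2.46% | 1.87 |

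**Step 2. Effect on the log-rank test.** A simulation used all three GRACE groups, no treatment effect, two groups of 178 and 177, two-sided 5% and 2000 runs per setting. Risks were taken as quoted, then scaled so that overall mortality was 6.7% or 10.4%.

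| Assumed low/moderate/high mix | Apparent crude HR | Crude log-rank rejects: quoted risks | at 6.7% | at 10.4% |
|---|---|---|---|---|
| 50/30/20 v 20/30/50 | about 1.5 | 10% | 16% | 23% |
| 60/30/10 v 10/30/60 | 1.9 to 2.0 | 19% | 35% | 51% |

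Stratifying by GRACE group brought rejection back to about 3% to 6% in every setting. That is a best case, because the stratifier was the only source of risk difference in the simulation.

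**Step 3. Can an adjusted model be fitted?**
- Expected deaths: 355 × 0.067 = 23.8; 355 × 0.104 = 36.9.
- Parameters: three strategy indicators plus one score = 4.
- Deaths per parameter: 23.8 / 4 = 5.9; 36.9 / 4 = 9.2.

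This supports one summary score, not a long covariate list.

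**Step 4. Precision.** Assume deaths split equally over four groups. For one pair, SE(log HR) ≈ √(1/d + 1/d).
- d = 24/4 = 6: SE = 0.577, and exp(1.96 × 0.577) = 3.1.
- d = 37/4 = 9.25: SE = 0.465, and exp(1.96 × 0.465) = 2.5.

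An estimated hazard ratio of 1.0 would carry a 95% interval of roughly 0.3 to 3.1, or 0.4 to 2.5.

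**The case against.** **The Cox model may already cover this.** The article does not list its covariates. Revascularisation data are captured at baseline, and the sentence after the log-rank sentence promises hazard ratios for all variables, which Kaplan-Meier and log-rank do not supply. An adjusted strategy comparison may be intended. The article does not say so, however: the model's stated purpose is baseline predictors, and the method stated for the reperfusion groups is the crude one.

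**The objective can be answered descriptively.** This stands. The objective asks for a comparison of outcomes between patients who received each strategy, and a log-rank test answers whether crude survival differs. A reader might infer that the objective cannot be answered at all. The documents do not support that; what fails is the step to treatment benefit.

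**The size is assumed.** This also stands. No mix comes from the article, the risks are predicted medians, and the two-group calculations stand in for four groups of unknown size. The 51% rejection rate needs both the more extreme mix and the higher mortality. The milder mix at the quoted risks gives 10%.

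**GRACE is not a full remedy.** This stands as well. Nothing in the article shows that it captures delay, contraindications or access. The Background describes two versions with different inputs and horizons, and Data collection does not say which is recorded. A reader might also infer that age and shock drive treatment choice here. The article names older age and heart failure as predictors of death, but does not describe age or shock as determinants of reperfusion.

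**Conclusion.** The point holds for one secondary objective. The analysis stated for the reperfusion groups is unadjusted, no sentence ties the planned multivariable model to that contrast, and the abstract and hypothesis give the comparison a treatment-benefit reading that a crude test cannot support.

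Under the assumed mixes, case-mix alone gives mortality ratios of 1.3 to 1.9. These figures show what is possible; they do not predict this cohort.

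Two stronger readings should be resisted. The plan is not without any multivariable analysis. Nor are the historical survival figures by reperfusion group in the Background shown to be confounded, since that registry's adjustment cannot be seen from this document. The primary objective, the all-cause mortality rate, is unaffected. This is a should-fix, not a must-fix.

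**What to change.** In Statistical analysis:

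1. Base conclusions about reperfusion strategy on a Cox model with reperfusion group plus the admission GRACE score as one continuous covariate. Report adjusted hazard ratios with 95% confidence intervals.
2. Name the GRACE version used.
3. Keep the crude Kaplan-Meier curves and the log-rank test, labelled as description.
4. Word conclusions as associations. State that delay, contraindications, access and other factors not captured by the score remain, and that a non-significant result does not show similar benefit.

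The cost is about one paragraph of text and no new data. The limitation is precision: with about 24 to 37 expected deaths and four parameters, the intervals will be wide and should be reported as such. Adjustment reduces bias from measured risk only.

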## Abstract

**Background:**

ST-segment elevation myocardial infarction (STEMI) is a clinically distinguishable yet lethal sequela of ischaemic heart disease (IHD). In sub-Saharan Africa (SSA), death due to acute STEMI is increasing. In South Africa, there is a paucity of data available on the clinical outcomes of acute STEMI within one year for individuals treated in the public healthcare sector. This study primarily seeks to determine the one-year all-cause mortality rate of acute STEMI. The study also assesses the value of serum cardiac biomarkers of myocardial damage and serum uric acid in predicting all-cause mortality in STEMI.

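### Every p < 0.05 counts as significant, although at least 32 secondary reperfusion comparisons and three biomarker analyses are planned and none is named as the lead or marked exploratory

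*Protocol article*

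**What the plan says.** All references are to the protocol article.

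- **Decision rule** (Statistical analysis): "For all tests, a p-value < 0.05 will be considered statistically significant".
- **Primary objective** (Study aims): "To determine the all-cause mortality rate of an acute STEMI at 30 days, three and six months, and one year after the index presentation". This is a rate to be estimated, not a contrast to be tested.
- **Further outcomes** (Study aims, secondary): "To determine the rates of cardiac-related re-hospitalisation, heart failure, angina, major bleeding, thromboembolism, non-fatal arrhythmias", followed by "planned or unplanned repeated revascularisation at 30 days, three and six months and one year after the index STEMI".
- **Reperfusion comparison** (Study aims, secondary): "To compare the clinical outcomes between STEMI patients who received thrombolysis, PCI, a pharmaco-invasive strategy and those who underwent no reperfusion at 30 days", and at the three later time points.
- **Biomarkers** (Study aims, secondary): "To assess the relationship between all-cause mortality and the peak serum hs-cTnT, CRP and SUA measured on admission".
- **Intended use** (abstract, Discussion): "By comparing the clinical outcomes between the different coronary reperfusion strategies, our results may guide clinicians in providing better patient treatment". The abstract and the main Discussion also put forward uric acid as a low-cost prognostic marker.

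Two other places bear on the point. The Statistical analysis section plans Kaplan-Meier curves of crude one-year survival by reperfusion group with log-rank tests. The last paragraph of the Background expects similar one-year mortality and morbidity for three active strategies: fibrinolysis, primary PCI, and fibrinolysis followed by PCI. Neither place says that the log-rank test leads the other comparisons.

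**The concern.** The rule gives every test the same standing. A difference in, say, major bleeding at three months that reaches p = 0.04 is as significant under the plan as a difference in one-year mortality. With this many tests, some will cross 0.05 by chance even where nothing differs. Different outcomes or time points may also point in opposite directions, and the plan does not say which one counts.

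This matters because the article does not present the comparisons as purely descriptive. It links them to treatment choice and to routine use of a biomarker. An isolated result could be reported as support for either.

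The complaint concerns a rule that the article states, not something it leaves out. It is separate from confounding between reperfusion groups and from the number of deaths available per model.

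**Working it through.** The article states no error rate across tests, so there is no figure of its own to reproduce.

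**1. Count of tests.** Outcomes in the Study aims: death, cardiac re-hospitalisation, heart failure, angina, major bleeding, thromboembolism, arrhythmia and repeat revascularisation, which makes 8. Time points: 30 days, three months, six months, one year, which makes 4. One overall four-group test each gives 8 × 4 = 32. This is a minimum: four groups allow six pairwise contrasts per outcome and time, and the predictor analyses at four time points come on top.

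**2. Expected false positives if all are null.** 32 × 0.05 = 1.6, whatever the correlation between tests.

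**3. Upper reference, independent tests.** 1 − 0.95^32 = 0.806. This is too high, because cumulative outcomes at successive times overlap.

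**4. Allowing for correlation.** I simulated 32 chi-square statistics with 3 degrees of freedom, each tested at 0.05, with no true differences.

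- Correlation between time points was taken as √(p_early / p_late). The rates 2.4% (30 days) and 6.7% (one year) come from the South African registry cited in the Background. The values 4% and 5% in between are assumed. For 30 days against one year this gives √(0.024 / 0.067) = 0.60. The same pattern was used for all eight outcomes.
- Correlation between outcomes is not in the document and was varied.

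| Between-outcome correlation (assumed) | Chance of at least one false positive, 32 tests |
|---|---|
| 0 | 0.64 |
| 0.3 | 0.59 |
| 0.5 | 0.51 |
| 0.7 | 0.41 |

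Mortality alone at the four times gives 0.12.

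**5. Only the three active strategies.** The same calculation with 2 degrees of freedom gives 0.64, 0.58, 0.51 and 0.40. Leaving out the no-reperfusion group hardly changes the result.

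**6. Three biomarkers at one year.** Independent: 1 − 0.95³ = 0.143. At correlation 0.3, 0.5 and 0.7: about 0.14, 0.13 and 0.11.

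**7. Cross-check of a related quantity.** A patient-level simulation used 355 patients, binary cumulative outcomes with assumed one-year rates of 5% to 25%, and between-outcome correlation from 0 to 0.5 on an underlying latent scale. The 32 tests together with three independent biomarker tests gave 0.59 to 0.71. Adding the six pairwise tests per outcome and time gave about 0.95 to 0.99. These figures cover more tests and stop at a lower correlation, so they do not replace the table.

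**The case against.** **A false positive is more likely than not.** A reader might infer this, but the documents do not support it as a flat statement. It needs every comparison to be null and the between-outcome correlation to be no higher than about 0.5; at 0.7 the figure is 0.41. The Background itself cites a French registry with one-year survival of 78.5% without reperfusion, against 93.6% with thrombolysis and 91.8% with primary PCI (p < 0.001). The null is therefore implausible for no reperfusion against treatment. It is less strained among the active strategies, where the authors themselves expect no difference.

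**There is no hierarchy at all.** This also goes too far. The aims separate one primary objective from the secondary ones, and the analysis section singles out one-year survival by log-rank test for the reperfusion groups. What stands is that secondary does not mean exploratory, and that the log-rank test is not given precedence over the other comparisons.

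**The abstract contradicts the Methods on the primary time point.** The abstract says "This study primarily seeks to determine the one-year all-cause mortality rate of acute STEMI", and the aims list four times including one year. That is condensation, not a contradiction.

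**Multiplicity belongs in the analysis plan, and an observational cohort need not control it.** The first half would answer a complaint of silence, but the article fixes a threshold for all tests. The second half has force: whether formal adjustment such as Holm is needed for secondary analyses of a cohort is debatable. That argues for labelling and a named lead rather than adjusted p-values. The article also promises hazard ratios with 95% confidence intervals, which helps.

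**A four-group test would not answer the authors' question.** This stands. On the cited rates, one-year mortality is 21.5% without reperfusion against 6.4% and 8.2% with treatment, so the untreated group could drive the result. The lead test should therefore focus on the active strategies.

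**Conclusion.** The point holds in limited form. The significance rule is too broad for the number of secondary comparisons and for the use the article foresees for them.

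Under no true differences, the reperfusion comparisons carry a chance of about 0.41 to 0.64 of at least one false significant result. That is roughly 8 to 13 times the nominal 0.05 (0.41 / 0.05 = 8.2; 0.64 / 0.05 = 12.8). The three biomarkers at one year carry about 0.11 to 0.14.

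These figures rest on assumed between-outcome correlations, two assumed intermediate event rates, one overall test per outcome and time, and valid individual tests. Where some differences are real, fewer tests can give false positives and the risk is smaller. The primary objective, an estimated mortality rate, is untouched. The matter is worth correcting but does not threaten the study's main result.

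**What to change.** In the Statistical analysis section, replace the sentence on significance with text to this effect:

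- The lead reperfusion comparison is the planned log-rank test of one-year all-cause mortality at two-sided 0.05. It is restricted to, or reported separately for, the three active strategies in the Background hypothesis (fibrinolysis, primary PCI, fibrinolysis followed by PCI). The contrast with no reperfusion is reported separately.
- For the biomarker objective, the endpoint is one-year all-cause mortality, with one lead marker. Uric acid is the natural candidate, since the abstract and Discussion single it out.
- All other outcomes, time points, markers and predictor analyses are exploratory and reported as estimates with 95% confidence intervals, without declaring significance.

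Each of the two objectives then has one test at 0.05. Because the authors expect the strategies to be similar, the lead comparison should be read through its hazard ratios and intervals; a non-significant result would not by itself show similarity.

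The change needs no new patients or data and does not touch clinical management. Its cost is that fewer results can be called significant.
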